## Abstract

**Background:**

Responsive infant feeding occurs when a parent recognizes the infant’s cues of hunger or satiety and responds promptly to these cues. It is known to promote healthy dietary patterns and infant weight gain and is recommended as part of the Dietary Guidelines for Americans. However, the use of responsive infant feeding can be challenging for many parents. Research is needed to assist caregivers recognize infant hunger or satiety cues and overcoming barriers to using responsive infant feeding.

**Objective:**

The Learning Early Infant Feeding Cues (LEIFc) intervention was designed to fill this gap by using a validated coaching approach, SS-OO-PP-RR (“super,” Setting the Stage, Observation and Opportunities, Problem Solving and Planning, Reflection and Review), to promote responsive infant feeding. Guided by the Obesity-Related Behavioral Intervention Trials model, this study aims to test the feasibility and fidelity of the LEIFc intervention in a group of mother-infant dyads.

**Methods:**

This pre-post quasi-experimental study with no control group will recruit mothers (N=30) in their third trimester (28 weeks and beyond) of pregnancy from community settings. Study visit 1 will occur prenatally in which written and video material on infant feeding and infant hunger and satiety cues is provided. Demographic information and plans for infant feeding are also collected prenatally via self-report surveys. The use of responsive infant feeding via subjective (survey) and objective (video) measures is recorded before (study visit 2, 1 month post partum) and after (study visit 5, 4 months post partum) intervention. Coaching on responsive infant feeding during a feeding session is provided by a trained interventionist using the SS-OO-PP-RR approach at study visits 3 (2 months post partum) and 4 (3 months post partum). Infant feeding practices are recorded via survey, and infant weight and length are measured at each postpartum study visit. Qualitative data on the LEIFc intervention are provided by the interventionist and mother. Infant feeding videos will be coded and tabulated for instances of infant cues and maternal responses. Subjective measures of responsive infant feeding will also be tabulated. The use of responsive infant feeding pre-post intervention will be analyzed using matched *t* tests. Qualitative data will be examined to guide intervention refinement.

**Results:**

This study initially began in spring 2020 but was halted because of the COVID-10 pandemic. With new funding, recruitment, enrollment, and data collection began in April 2022 and will continue until April 2023.

**Conclusions:**

After refinement, the LEIFc intervention will be tested in a pilot randomized controlled trial. The long-term goal is to implement LEIFc in the curricula of federally funded maternal-child home visiting programs that serve vulnerable populations—those that often have infant feeding practices that do not align with recommendations and are less likely to use responsive infant feeding.

**International Registered Report Identifier (IRRID):**

DERR1-10.2196/44329

## Introduction

Infant feeding practices, which include what and how infants are fed, contribute to infant growth and development, and thus, lifelong health [1]. Specifically, healthy infant feeding practices contribute to a healthy weight gain trajectory, which has been associated with decreased obesity later in life [2,3]. Healthy infant feeding practices include not only *what* infants are fed but also *how* infants are fed. The introduction of breastfeeding, breastfeeding until at least 6 months of age, introduction of complementary foods around 6 months and not before 4 months of age, and avoidance of juice and sugar sweetened beverages are recommended examples of *what* infants should be fed [1,4]. The responsive feeding approach is recommended for *how* infants should be fed and has been associated with healthy infant weight gain trajectories [4].

Responsive feeding occurs when a parent (or other caregiver) learns and recognizes the infant’s cues of hunger and satiety (Textbox 1) and responds promptly to these cues [5]. Responsive feeding is thought to promote the ability to recognize and respond to internal cues of hunger and satiety [6-10]. This ability to recognize these internal cues and self-regulate intake in response to physiologic need is associated with healthy weight gain during infancy as well as dietary behaviors later in life [8,11]. For these reasons, it is important that parents use the responsive feeding approach when feeding their infant.

Hunger and satiety cues in infants less than 6 months [5,7].
**Hunger signals**
Wakes up and increased alertnessMoves aroundSmacks lipsSucks on fist and fingersCries or fussesOpens mouth wideResponse to rooting reflex
**Satiety signals**
Seals lipsTurns head awayDecreases or stops suckingSpits out nippleFalls asleepDecreased muscle tone

Three things must be in place for responsive feeding to occur: (1) the child signals hunger; (2) the caregiver recognizes cues and responds promptly; and (3) the child experiences a predictable response to hunger [5]. For this process to occur, caregivers must read their child’s nonverbal cues and respond contingently. The degree to which a caregiver responds contingently to a child’s communication, whether it is to a child’s hunger cues or to bids for social interaction, is widely known to predict a child’s language development [12-14]. As such, coaching caregivers to respond to feeding cues could impact overall caregiver responsiveness to their child’s communication bids, which could support the child’s early language development by extension.

Interventions to promote responsive feeding have shown benefit in preventing rapid infant weight gain and promoting healthy dietary patterns in infants and young children [15-22]. Despite the correlation between responsive feeding and healthy infant weight gain, the successful use of responsive feeding by caregivers is still lacking [23]. Caregivers report that recognition of hunger and satiety cues in their infant is challenging [24,25]. Infant cues can be subtle, and it can be difficult for parents to differentiate reflexive movements such as hand to mouth and rooting. Additionally, recent literature has identified maternal characteristics such as infant feeding beliefs, age, mental health, and the mother’s own eating behavior as contributing to the use of responsive feeding [26-29]. Infant temperament and support from health care professionals and family and friends also play a role [23,26]. Therefore, more research is needed to find ways to assist caregivers in recognition of hunger and satiety cues and to overcome additional barriers to promote the use of responsive feeding during infancy.

The Learning Early Infant Feeding Cues (LEIFc) intervention was designed to fill this gap by using a validated coaching approach with the mothers of new infants to promote responsive feeding. The proposed study aims to test the feasibility and fidelity of the LEIFc intervention in a group of mother-infant dyads. We aimed to (1) develop, refine, and test a responsive feeding intervention that can be used within real-world settings to serve mother-infant dyads in the community and (2) design the model with a primary emphasis on responsive feeding, but with a secondary focus on early communication to help caregivers understand the dual benefit of noticing and responding to infant cues.

## Methods

### Ethics Approval

The institutional review board at Florida State University approved this study (STUDY00002895).

### Theoretical Framework

The Obesity-Related Behavioral Intervention Trials (ORBIT) model is used to guide the proposed study [30]. The ORBIT model uses an iterative process and was chosen because the LEIFc intervention is behavioral in nature, in the early stage of development, and focused on prevention of a chronic disease [30]. Testing fidelity and feasibility of the LEIFc intervention study falls into phase I of the ORBIT model as the intervention has been designed but needs to be refined based on preliminary testing. The findings from this initial study will provide the foundation to move to phase II and conduct a proof-of-concept trail.

### Study Design and Intervention

This study uses a pre-post quasi-experimental design with no control group to examine the feasibility, fidelity, and social validity of the LEIFc intervention. The intervention was developed based on existing literature regarding enablers and barriers to the use of responsive feeding by caregivers and communication cues present early in life. The multicomponent LEIFc intervention involves maternal education on responsive feeding practices and mother-infant communication while using a family-guided caregiver coaching approach called SS-OO-PP-RR (“super,” Setting the Stage, Observation and Opportunities, Problem Solving and Planning, Reflection and Review) during feeding sessions [31,32]. The SS-OO-PP-RR approach was developed based on adult learning theory and has been successfully used with parents and childcare providers to promote development across domains in infants and young children [31-33]. For the LEIFc intervention, SS-OO-PP-RR was modified to be specific to communication during feeding to promote responsive feeding (Textbox 2). It is used as a guide for the interventionist during the coaching session but will also be used to evaluate the fidelity of the intervention. The objective measure of responsive feeding will occur through video recording of feeding sessions between mothers and infants. Videos will be coded before the intervention and then after 2 coaching sessions between the interventionist and the mother during a feeding session. The subjective measure of responsive feeding will be collected via a self-report questionnaire completed by mothers before and after the intervention study visits.

The “super,” Setting the Stage, Observation and Opportunities, Problem Solving and Planning, Reflection and Review intervention.
**Setting the Stage (SS)**
Asks the caregiver to update how responsive feedings have been going since the last visit—listens, encourages caregiver reflection, and sets up problem-solving as neededShares information related to responsive feeding—connects strategies to the child’s long-term health, well-being, and communication developmentClarifies responsiveness strategies to use during the session (watching for hunger and fullness cues, using talk and touch during feeding, and stopping when the baby is full)
**Observation and Opportunities to Embed (OO)**
Observes the caregiver-child interaction in feeding routine—provides feedback and builds on dyad strengthsUses coaching strategies (guided practice, direct teaching, demonstration, and caregiver practice) to help the caregiver embed responsiveness strategies into the feeding routineProvides general and specific feedback on caregiver and child behaviors and interactions (links caregiver strategy to child response)
**Problem-Solving and Planning (PP)**
Problems solved with the caregiver about appropriate responsive feeding strategiesSupports the caregiver to identify opportunities to help other caregivers use the strategies (other parents, childcare, and grandparents)
**Reflection and Review (RR)**
Asks questions and comments to promote caregiver reflection and review of the feeding routine—identifies what worked for the caregiver and childEngages the caregiver to lead development of a “best plan of action” for using responsiveness strategies between visits

### Setting and Participants

Mothers of any parity will be recruited from community settings during the third trimester (28 weeks and beyond) of a healthy pregnancy. To be eligible, mothers need to be aged 18 years or older, able to read and speak English, and agree to video recording of an infant feeding in their home. Any medical or congenital condition in the fetus that would interfere with infant feeding or growth (ie, Down syndrome or cleft lip or palate) will be excluded. Mothers will be enrolled in the third trimester and then screened again after the birth of the infant to ensure that mother and infant remain eligible to participate.

An interventionist will be recruited to deliver the LEIFc intervention in the homes of new mothers. He or she will ideally have a background in maternal-child health and may be a nurse, social worker, speech-language pathologist, dietician, or early child development specialist. The interventionist will be trained on the SS-OO-PP-RR approach and the LEIFc protocol. Because the purpose of this study is to test the fidelity and feasibility of the intervention, feedback from the interventionist will be sought as part of the research protocol.

### Procedures

Eligible mothers will be identified through community settings such as obstetrician offices, prenatal parenting or birth classes, social media forums that pregnant moms may frequent, and word of mouth. If eligible and interested in the study, study personnel will consent mothers for the study. Once enrolled in the study, the interventionist will implement each study visit (Table 1). Study visit 1 is conducted when the mother is in the third trimester of pregnancy. Written material on infant feeding and infant cues of hunger and satiety is provided. Additionally, 2 short videos, one on infant hunger cues and the second on infant satiety cues, are watched with the interventionist and the mother. Any questions on feeding or communication are answered by the interventionist. Study visit 2 is conducted when the infant is approximately 1 month old. At this visit, a video recording of a feeding session between the mother and the infant is taken with no interaction with the interventionist. The feeding can be from the breast or from the bottle (with breastmilk or formula). Study visits 3 (at infant age of 2 months) and 4 (at infant age of 3 months) are the intervention study visits. At each visit, the interventionist will use the SS-OO-PP-RR tool to coach the mother through the feeding to identify hunger and satiety cues and discuss ways to respond. Each of these visits is also video recorded. The final study visit is at infant age of 4 months when another video recording of the infant feeding session is taken with no coaching from the interventionist.

At study visit 1, demographic data are collected along with the mother’s prenatal plans for infant feeding. At study visit 2, birth history is collected along with infant feeding practices, and the mother completes the Infant Feeding Questionnaire (IFQ). During study visits 3 and 4, infant feeding practices are collected. At study visit 5, the mother completes the IFQ and provides feedback on the study itself through a series of qualitative questions.

**Table 1 table1:** Timing of study visits and procedures.

Study visit	Timing of visit	Components of the visit	Visit location
1	Prenatal (28 weeks or beyond of gestation)	Education provided on communication with your baby during feeding—videos and written material	Video conferencing platform (Zoom)
2	Infant age approximately 1 month	Complete Infant Feeding Questionnaire Video record the mother and baby during a feeding with no coaching Collect current infant feeding practices	Family home
3	Infant age approximately 2 months	Video record the mother and baby during a feeding Provide coaching to the mother during the feeding Collect current infant feeding practices	Family home
4	Infant age approximately 3 months	Video record the mother and baby during a feeding Provide coaching to the mother during the feeding Collect current infant feeding practices	Family home
5	Infant age approximately 4 months	Video record the mother and baby during a feeding with no coaching Complete Infant Feeding Questionnaire Collect current infant feeding practices	Family home

### Outcome Measures

The primary outcome in this study is the use of responsive feeding. This will be measured before (study visit 2) and after (study visit 5) intervention. Data are obtained subjectively through evaluation of the IFQ and objectively through a video review. The IFQ will provide a subjective measure of responsive feeding. This 20-item self-report tool has been validated for use in mothers of infants [29,34,35]. Likert-type scoring is used; higher scores indicate a stronger measure of the construct. Three subscales will be used to measure responsive feeding: use of food to calm, use of food to soothe, and awareness of infant cues.

The objective measure of responsive feeding will be collected via coding of the video session before and after intervention. The research team developed a coding scheme to capture both mother and infant behaviors during the feeding interactions. The coding scheme was adapted from the Responsiveness to Child Feeding Cues Scale [36] to define specific, discrete maternal behaviors that relate to responding to infant hunger and satiety cues as well as early infant communication acts. Infant behaviors are coded for hunger, satiety, and early communication acts. Research assistants will be trained on the coding scheme and will use existing videos to code with a goal of at least 85% agreement achieved to confirm inter-rater reliability. The coding scheme developed by the team will be used to code the feeding interactions for study visits 2 and 5. Videos will be coded for the number and rate of maternal utterances directed toward the child and responsiveness to the child’s vocalizations using the Noldus Observer XT software. The percentage of the interactions spent jointly engaged between the mother and the infant will also be coded.

Infant feeding practices, demographic characteristics (ie, maternal age, marital status, education level, and race and ethnicity), and maternal depression will be considered as covariates. Initiation and duration of breastfeeding and age at complementary food introduction will be extracted from data and tabulated into variables: duration of breastfeeding (any and exclusive) calculated in weeks and age at complementary food introduction calculated in weeks. Demographic data are collected at study visit 1, infant feeding practices at study visits 2 through 5, and maternal depression (via the Patient Health Questionnaire-9) at study visits 2 through 5.

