### Statistical Analyses

Power analysis for the matched-pair *t* test was conducted. With the lower limit of the medium effect size of 0.5 [37], sample sizes of 27 and 36 provided 80% and 90% power, respectively, under 1-sided directional null hypothesis and the nominal significance rate of .05. We will aim to enroll 30 participants for this feasibility and fidelity study.

Once data are clean, descriptive statistics will be computed and examined. For the primary outcome, benefit will be determined by an increase in responsive feeding codes pre-post SS-OO-PP-RR coaching sessions (visits 2 and 5). IFQ subscale scores will be analyzed using matched sample *t* tests for pre-post coaching sessions to determine the benefit of the intervention. If the assumptions of statistical tests are not clearly met, the Mann-Whitney *U* test would be considered as an alternative. In a future pilot randomized controlled trial (RCT), analysis of covariance (ANCOVA) will be conducted where the difference between treatment and control groups for the postmeasure is examined with the premeasure as a covariate. The use of ANCOVA provides a statistical control in addition to the design control for the premeasure via random assignment in the RCT.

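### The stated purpose is feasibility, fidelity and social validity, but the only named primary outcome, the sample size and the success rule concern uncontrolled change in responsive feeding

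*Protocol article*

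**What the plan says.** **Purpose.** The end of the Introduction states: "The proposed study aims to test the feasibility and fidelity of the LEIFc intervention in a group of mother-infant dyads". Study Design and Intervention says that the single-group pre-post design is used "to examine the feasibility, fidelity, and social validity of the LEIFc intervention". Setting and Participants repeats the point ("Because the purpose of this study is to test the fidelity and feasibility of the intervention"), and so do the Abstract and the Conclusions. Theoretical Framework places the study in ORBIT phase I.

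**Primary outcome.** Outcome Measures states: "The primary outcome in this study is the use of responsive feeding". It is measured at visit 2 and visit 5 by the IFQ and by coded video.

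**Sample size and success rule.** Statistical Analyses bases the sample size on a matched-pair t test with effect size 0.5 and one-sided 5% significance. For the primary outcome, "benefit will be determined by an increase in responsive feeding codes pre-post SS-OO-PP-RR coaching sessions (visits 2 and 5"). The IFQ subscales get matched-sample t "tests for pre-post coaching sessions to determine the benefit of the intervention".

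**Limit on inference.** Anticipated Findings says that any pre-post change cannot be credited to the intervention until a controlled trial has been run.

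**What is planned for the stated aims.** Study Design and Intervention names the SS-OO-PP-RR tool for evaluating fidelity. Procedures says that coaching visits 3 and 4 are video recorded. Mothers give qualitative feedback at visit 5 and the interventionist at visits 3 and 4, for use in refining the intervention.

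**The concern.** The outcome labelled primary does not measure any of the three things the study says it is for. It measures whether mothers' feeding behavior changes. With one arm, that change mixes any effect of coaching with everything else that happens as the infant goes from about 1 to about 4 months of age.

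Two things are at stake. First, the quantities that 30 dyads in one arm can estimate directly (how many complete the visits, and how fully the coaching is delivered) have no primary status, although Theoretical Framework and Conclusions present this study as the basis for the next ORBIT phase. Second, Statistical Analyses and Anticipated Findings give incompatible instructions for reading the same result: one treats an increase as showing benefit, the other says it cannot be credited to the intervention.

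**Working it through.** **Step 1: what the sample size was built for.** Inputs from Statistical Analyses: d = 0.5, one-sided alpha = 0.05, stated n = 27 (80% power) and n = 36 (90% power), planned enrollment 30.

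Formula: power = P(T > t₀.₉₅,ₙ₋₁), where T is noncentral t with n − 1 degrees of freedom and noncentrality d√n.

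| n | d√n | Power |
|---|---|---|
| 26 | 0.5 × √26 = 2.550 | 79.8% |
| 27 | 0.5 × √27 = 2.598 | 81.2% |
| 30 | 0.5 × √30 = 2.739 | 84.8% |
| 36 | 0.5 × √36 = 3.000 | 90.3% |

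The smallest n reaching 80% is 27 and the smallest reaching 90% is 36, as stated. The arithmetic is right. It shows that the number of dyads follows from a test of change; no figure in the section concerns feasibility or fidelity. The 84.8% at n = 30 assumes that every dyad completes. More than three losses leave at most 26 pairs, just below 80%.

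**Step 2: aim against outcome.**

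| Stated aim | Planned data | Named as primary? |
|---|---|---|
| Feasibility | Visits held; interventionist feedback at visits 3 and 4 | No |
| Fidelity | SS-OO-PP-RR tool; recordings of visits 3 and 4 | No |
| Social validity | Mothers' feedback at visit 5 | No |
| (not a stated purpose) Change in responsive feeding | IFQ and coded video, visits 2 and 5 | Yes, the only one |

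**Step 3: benefit against attribution.** Statistical Analyses takes the visit 2 to visit 5 change as the measure of benefit. Anticipated Findings rules out attributing that change to the intervention. Both cannot guide the interpretation of the same comparison. The second agrees with a design that has no control group.

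**Step 4: what 30 dyads can say about feasibility.** The article gives no target rate, so the completion rates below are assumptions. Exact (Clopper-Pearson) 95% limits for k of n are the 2.5% quantile of Beta(k, n − k + 1) and the 97.5% quantile of Beta(k + 1, n − k).

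| Completing visits 2–5 | 95% CI |
|---|---|
| 21/30 (70%) | 51% to 85% |
| 24/30 (80%) | 61% to 92% |
| 27/30 (90%) | 73% to 98% |

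**Step 5: what the coaching recordings can say about fidelity.** Two coaching visits per dyad give up to 30 × 2 = 60 sessions. Assume for illustration that 80% meet a fidelity standard. If sessions were independent, 48/60 gives 68% to 89%. The design effect for pairs is 1 + (2 − 1)ρ. With ρ = 1 it equals 2, the effective number is 60/2 = 30, and the interval is that of 24/30: 61% to 92%. The precision lies between these two. Scoring single components within sessions adds a further level of clustering, so a simple exact binomial interval on the component count would probably be too narrow.

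**The case against.** The strongest reply is that the article does plan for its stated aims. A fidelity tool is named, the coaching visits are recorded, and feedback from mothers and the interventionist feeds refinement. Scoring rules, raters and progression thresholds are details that a condensed article may leave to the full protocol or analysis plan. All of this stands, and their absence is not the point made here. It does not remove the mismatch: the article says which outcome is primary, and it is not one that the aim calls for. A fuller document could not change that without contradicting Outcome Measures.

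Four stronger readings are tempting, and the article does not support them:

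- *That fidelity goes unscored.* The sentence "The coding scheme developed by the team will be used to code the feeding interactions for study visits 2 and 5" concerns the scheme for maternal and infant behavior, for which uncoached feedings before and after coaching are the proper measurement points. Fidelity has its own tool.
- *That the study cannot answer its question.* The relevant data are to be collected; they lack primary status.
- *That a p-value decides progression.* No section says so. Conclusions refers to the results of the feasibility study as a whole, and Anticipated Findings ties refinement to the qualitative data.
- *That mothers' feedback is biased by courtesy.* Procedures says "Once enrolled in the study, the interventionist will implement each study visit", but how the visit 5 questions are asked and returned is not stated, so bias is only a possibility.

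Timing is also a fair objection: data collection is under way, so changing the primary outcome is a mid-study amendment.

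**Conclusion.** The point holds in a limited form and should be corrected before analysis. The purpose is given consistently as feasibility and fidelity, with social validity added in Study Design and Intervention. The single primary outcome, the sample size and the quantitative success rule all concern uncontrolled change in responsive feeding. Separately, the benefit wording in Statistical Analyses conflicts with the statement on attribution in Anticipated Findings.

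This is a mismatch of designation and interpretation, not a numerical error: the power figures are correct for the test described. The intervals for completion and fidelity rest on assumed rates. They show the precision available from 30 dyads, wide but usable (61% to 92% at 80% completion), and do not measure the size of any error.

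**What to change.** 1. **Name two primary outcomes.** (a) The proportion of enrolled dyads completing visits 2 to 5, with an exact 95% CI. Because mothers are screened again after birth, say whether those who become ineligible stay in the denominator. (b) SS-OO-PP-RR fidelity at visits 3 and 4, scored by research assistants from the recordings, with an interval that allows for clustering of components within sessions and of sessions within dyads (for example, a bootstrap that resamples dyads). If one interventionist delivers all the coaching, say that the result describes that person's delivery.
2. **Set progression criteria** for both outcomes before anyone looks at the data. The values are for the sponsor to choose; the article gives no basis for particular cut-offs.
3. **Make change in responsive feeding secondary.** Keep the visit 2 and visit 5 coding and the IFQ, and report the mean change with a confidence interval. Leave IFQ collection the same at both visits, since altering the mode at visit 5 alone would build a mode difference into the comparison.
4. **Reword Statistical Analyses** so that the pre-post comparison describes change and no longer determines benefit, in agreement with Anticipated Findings. Justify the 30 dyads by the precision of the primary outcomes; the existing power statement can stay for the secondary one.
5. **Keep the qualitative feedback** as planned, as the descriptive evidence on social validity.

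Cost: research-assistant time to score up to 60 recordings, and an amendment, dated and documented because the study is ongoing, that records which data had been seen when it was made. No new visits are needed.
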